## Discussion

The efficacy of single-implant mandibular overdentures to stabilize CDs in edentulous patients has been noted recently [23]. This form of implant therapy is expected to become one of the main treatments for edentulous patients because it involves the insertion of only one implant and thus less surgical invasion and is highly convenient. However, it is difficult to apply this approach in geriatric patients who have systemic diseases or are unable to visit the hospital, and a fundamental solution to this problem has not yet been identified.

In clinical dentistry, the supplementary use of RL materials in the postoperative management of CD wearers has already been recognized [24–26]. Since their introduction in the 1950s, these RL materials have been used to improve the fit of CDs, condition traumatized tissues, and provide an interim or permanent cushioning-like effect. These materials have been reported to help distribute the forces of mastication more evenly and absorb energy [5, 24]. However, most of the previous studies on RL materials have focused on their material properties, including their mechanical properties, the bond strength between the denture resin and the RL, and bonding methods [5]. In contrast, few clinical trials have investigated the clinical effects of RL materials [7–13], and no large clinical study has been conducted to clarify the functionality of RL materials using a multicenter RCT, as in this trial.

In Japan’s rapidly aging society, many elderly CD wearers are unable to visit the dentist's office, despite the fact that poor denture quality can affect their quality of life. The application of RL materials can help some of these patients. However, the lack of sufficient evidence on RL materials has made dentists hesitant to recommend or apply them.

This clinical study has several limitations. First, both the patient and the dentist cannot be blinded to the dental treatment due to its nature. In this study design, it is not possible to conduct a double-blind study. Second, the results obtained have limited generalizability because the sample includes only patients who are able to visit the hospital. Since the external validity of the evidence is lacking as the society further ages, we believe it is necessary to conduct a clinical trial in a new population.

The RCT will provide dentists and prosthetic educators evidence regarding the effectiveness of RL materials for edentulous patients. We believe that the evidence will liberate dentists from the conventional notion that RL materials cause more harm than benefit, and will yield useful information for selecting treatment options for edentulous patients with ill-fitting CDs.

## Trial status and results

The trial study period is January 2021–March 2024 (registration period until September 2023). At the time of manuscript submission (January 26, 2022), patient recruitment is ongoing.

The obtained data will be presented at relevant scientific conferences and submitted to academic journals to help develop diagnostic and therapeutic guidelines for the selection and use of resilient liners.

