**Methods:**

The study is currently being conducted at eight centers, and a parallel-group randomized controlled trial (RCT) is underway. One hundred thirty-two edentulous patients with poorly fitting mandibular CDs will be assigned to two groups based on whether they will receive RL or NRL. Participants will have an RL or NRL applied for relining their CDs using an indirect method of dynamic impressions. Data will be recorded at 1 week and 3, 6, and 12 months after denture delivery. The primary outcome will be assessment of the patients’ general satisfaction by using a 100-mm visual analog scale (VAS). Secondary outcomes will be measured as patient-reported outcomes, including food intake status and oral hygiene-related quality of life. Masticatory performance and the number of sore spots on the oral mucosa will also be recorded. Comparisons between the two groups and within-subject comparisons of pre- and post-intervention measurements will be conducted.

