### Outcomes

The basic patient information recorded will include age, sex, years of denture use, and number of dentures fabricated. In addition, treatment difficulty index measurements [14, 15] and evaluation of used dentures [16] will be performed. Since patient satisfaction with CDs is a clinically important factor for evaluating the therapeutic effect of CDs with RL, the primary endpoint will be patients’ overall satisfaction with the CDs, which will be determined using a 100-mm VAS [17]. Patient satisfaction will be assessed comprehensively using a questionnaire containing eight assessment items: general satisfaction, ease of speaking, ease of cleaning, retention, stability, comfort, and esthetics. Participants will be asked to rate their satisfaction with each item in the questionnaire by using a 100-mm VAS to evaluate their current CDs. Data will be recorded as continuous variables at 1-mm intervals by using calipers from the left end. Overall patient satisfaction will be measured four times: at baseline, 7 days, 3 months, 6 months, and 1 year.

In addition, to comprehensively understand the clinical effect of CDs with RL material, the Oral Health Impact Profile for edentulous subjects (OHIP-EDENT) [18], masticatory ability [19, 20], food intake [21, 22], and the location and number of mucosal pressure ulcers will be examined as secondary outcomes. Photographs of mucosal pressure ulcers will be shared among investigators to adequately calibrate assessments of the mucosal surface (Fig. 2).

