#### After 3, 6, and 12 months of wearing

The investigators evaluates patient satisfaction, chewing ability, OHIP-EDENT, and food intake.

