### Response to adverse events

The investigator, him or herself a dentist, will carefully monitor the occurrence of adverse events. If an adverse event occurs, appropriate measures will be taken and, in principle, the patients will be observed until the event disappears. The type of adverse event, date of occurrence (or date of hospital visit when discovered), details of treatment (continuation, discontinuation, etc.), course of the adverse event, and details of any causal relationship with the resilient liner will be promptly reported to the steering committee. Observations will continue up to 1 year after the application of the resilient liner and will continue throughout the study period.

In this study, there is no anticipated harm and compensation for trial participation.

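### Registration may run to September 2023 but the study period ends in March 2024, so late registrants cannot complete the planned 12-month follow-up within it

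*Protocol article*

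**What the plan says.** Under Trial status and results, the article gives the study period as "January 2021–March 2024 (registration period until September 2023".

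The follow-up horizon appears in four other places:

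- Abstract, Methods: "Data will be recorded at 1 week and 3, 6, and 12 months after denture delivery".
- Outcomes: "Overall patient satisfaction will be measured four times: at baseline, 7 days, 3 months, 6 months, and 1 year". The count of four does not match the five occasions listed, but the last one is one year in any case.
- Trial schedule: the final block of visits is headed "After 3, 6, and 12 months of wearing" and covers satisfaction, chewing ability, OHIP-EDENT and food intake.
- Response to adverse events: "Observations will continue up to 1 year after the application of the resilient liner".

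The Trial schedule section places the request for allocation at the initial visit and the fitting of the relined denture at the fourth. The 12-month clock therefore starts some time after registration. The article does not state how long this takes. The Intervention section mentions only an interval of about one week in connection with the tissue conditioner.

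**The concern.** A study that promises 12 months of follow-up needs at least 12 months between its last registration and its end. Here there are six, and nothing in the article shortens follow-up for late entrants or provides for visits after March 2024. A site could register a patient fully in line with the stated deadline and still be unable to carry out the stated schedule.

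At stake are the 12-month assessments of satisfaction and the secondary outcomes, the one-year adverse-event observation, and the follow-up study that the Background names as part of the trial's purpose. The loss would be built into the calendar and would come on top of ordinary dropout.

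**Working it through.** **The plan's own figure first.** The sample size rests on a 15 mm difference at 3 months, SDs of 26.3 and 31.4, two-sided 5% and 80% power (the 0.8 is printed as β and is read here as power).

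- Root-mean-square SD = √((26.3² + 31.4²)/2) = 28.96.
- n per arm = 2 × (1.960 + 0.842)² × 28.96² / 15² = 58.5, so 59, or 118 in total.
- With 10% dropout: 118 / 0.9 = 131.1, so 132.

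The target of 132 is reproduced. It depends on month 3 only.

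**Calendar inputs.** Registration ends 30 September 2023 and the study ends 31 March 2024, taking the last day of each stated month. Follow-up is 3, 6 and 12 months from delivery. *Assumption:* the lag from registration to delivery is 0 to 6 weeks.

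**Latest registration that still allows a visit by the study end** = 31 March 2024 − follow-up − lag.

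| Lag | Latest registration for month 12 | Latest registration for month 6 | Last registrant's month 3 | Last registrant's month 12 |
|---|---|---|---|---|
| 0 weeks | 31 Mar 2023 | 30 Sep 2023 | 30 Dec 2023 | 30 Sep 2024 |
| 3 weeks | 10 Mar 2023 | 9 Sep 2023 | 21 Jan 2024 | 21 Oct 2024 |
| 6 weeks | 17 Feb 2023 | 19 Aug 2023 | 11 Feb 2024 | 11 Nov 2024 |

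Month 3 fits for every registrant. Even with an 8-week lag the last 3-month visit falls on 25 February 2024. Month 6 just fits with no lag and fails for the last registrants with any lag of a few weeks. Month 12 fails for anyone registered after the dates in the second column.

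**Share affected at month 12.** *Assumption:* uniform accrual from 1 January 2021 to 30 September 2023, which is 1,002 days.

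- 0-week lag: 31 March to 30 September 2023 is 183 days; 183/1,002 = 18.3%, and × 132 = 24.1 patients.
- 6-week lag: 17 February to 30 September 2023 is 225 days; 225/1,002 = 22.5%, and × 132 = 29.6 patients.

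**Share affected at month 6.**

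- 3-week lag: 21/1,002 = 2.1%, or 2.8 patients.
- 6-week lag: 42/1,002 = 4.2%, or 5.5 patients.

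**Sensitivity to accrual.** If all 132 are registered by the cutoff in the second column, nobody is affected. If the accrual rate after the cutoff were 1.5 times the average (an illustration only), the count would be 1.5 × 24.1 = 36 to 1.5 × 29.6 = 44.

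**The case against.** The strongest reply is that the trial's main comparison is untouched. A reader might infer from the lost visits that the primary test or the sample size is compromised. The working shows otherwise: month 3 is reachable for the last possible registrant. Nor can one say that power at 12 months falls short of plan, because the article sets no effect size, SD or sample size for that time point. This part of the reply stands.

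Second, the patient count depends on accrual that the article does not describe. The registration date is an outer limit, and the article says only that recruitment was ongoing in January 2022. This also stands, and it is why the count is conditional. It does not remove the conflict between the dates, which needs no accrual assumption.

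Third, a reader might suspect bias between arms, or a loss concentrated in slow centres. Allocation is stratified by hospital in small blocks, so a calendar cutoff should remove similar numbers from both arms within each hospital. The article gives no accrual by centre, so nothing can be said about which centres would lose most.

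Fourth, other sections might soften the end date. Data handling ties formal termination partly to how data have accumulated, and Statistical analysis contemplates strategies for missing data. Neither sets visits beyond March 2024 or exempts late entrants. Response to adverse events also says that observation runs through the study period, but if that capped observation at March 2024 it would conflict with the one-year horizon in the same sentence.

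**Conclusion.** The point holds as an inconsistency between the registration deadline, the study end and the 12-month schedule. As printed, the three cannot all be met for anyone registered after about February–March 2023.

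Under uniform accrual and a 0–6 week lag, about 24 to 30 of 132 patients (18–22%) would lack a 12-month visit and a full year of observation within the study period. With a lag of 3 to 6 weeks, about 3 to 6 of them would also miss month 6. The possible range runs from none, if recruitment ends early, to more than 30 if accrual is back-loaded.

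The harm is to completeness and precision at 12 months and to the one-year safety observation. It does not reach the 3-month comparison, the target of 132 or its power, and a material imbalance between arms is not expected. This should be fixed, but it does not threaten the trial's main result.

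**What to change.** Reconcile the dates in one of these ways:

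1. Extend the study period to at least 12 months plus the time to delivery after the last registration. With registration open to 30 September 2023 and a 0–6 week lag, this means 30 September to 11 November 2024, so about October–November 2024.
2. Keep the March 2024 end and close registration by about 17 February to 31 March 2023, depending on the usual time to delivery.
3. If neither is possible, state that 12-month results cover only patients enrolled early enough to reach that visit. Treat later entrants as administratively censored, and report them separately from dropouts. The one-year adverse-event observation would need the same qualification.

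It would help to state the expected time from registration to delivery, since it determines the exact dates.

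The first option costs an administrative extension with ethics amendments at the participating universities, but no new patients or procedures. The second shortens the recruitment window by about six to seven and a half months and may put the target of 132 at risk. The third costs only wording but accepts the loss at 12 months.

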## Data Availability

The datasets analyzed during the current study and statistical code are available from the corresponding author on reasonable request, as is the full protocol.

## Abbreviations

CD: Complete denture
RL: Resilient liner
NRL: Non-resilient liner
MCORT II: Mandibular Complete dentures with Resilient liner Trial II
RCT: Randomized controlled trial
VAS: Visual analog scale
